# A web-based education program to encourage organ donation registration among lower-educated adolescents in the Netherlands: study protocol for a cluster randomized controlled trial

**DOI:** 10.1186/s13063-018-2927-6

**Published:** 2018-10-01

**Keywords:** Intervention, School, Organ donation, Registration, Adolescents, Internet

## Abstract

**Background:**

The gap between the supply and demand of organ donors is substantial, causing patients to suffer from long waiting times. Moreover, the lack of registrations places a burden on family members and medical professionals when an unregistered individual dies. This article describes a cluster randomized controlled trial (CRCT) study to assess the effectiveness and quality of implementation of a web-based program aimed at encouraging lower-educated adolescents to register a well-informed choice about organ donation, regardless of it being as a donor or not.

**Methods/design:**

The program will be delivered by teachers at schools for Intermediate Vocational Education in the Netherlands. The effectiveness will be assessed in a CRCT design with post-test only using self-administered questionnaires for the primary outcome (i.e. intention to register). Classes will be matched to improve equivalence of groups. From each pair of matched classes, one class will be randomly assigned to the experimental condition, and the other assigned to the control condition. Students in the control groups will fill in the questionnaire before receiving the program, while the experimental groups will do this afterwards. A post-test design prevents the risk of testing bias. The required sample size is 14 schools, with 10 classes per school and 13 unregistered students per class. The questionnaire assesses demographics, behavioural determinants (attitude, self-efficacy, knowledge and social outcomes), intention to register (as a donor) and registration status. Six months after delivery, registration status will be assessed again. Additionally, a process evaluation will be conducted to evaluate the quality of implementation using both qualitative (i.e. semi-structured interviews) and quantitative (i.e. logbooks, questionnaires, Google Analytics to track user behaviour at the website) methods.

**Discussion:**

Findings of the study can help to further improve the program and serve as a basis for a solid dissemination plan. Moreover, the study will provide insight into (change in) determinants of registration and donorship and the translation of research into practice of school-based health promotion interventions, which can serve as an example for others.

**Trial registration:**

The Dutch Trial Register, NTR6771. Registered on 24 October 2017. This is version 2 of the protocol (5 November 2017).

**Electronic supplementary material:**

The online version of this article (10.1186/s13063-018-2927-6) contains supplementary material, which is available to authorized users.

## Background

Despite an increase in the number of organ donors and successful transplantations in recent years, there is still a substantial gap between the supply and demand for organ donors. As a result, patients suffer from long waiting times or even die while waiting for an organ [1].

One of the many efforts to increase the number of registrations is a yearly initiative to encourage 18-year-olds to register their choice (irrespective of whether they want to be a donor or not). In the year after adolescents turn 18, they receive a letter from the Ministry of Health, Welfare and Sport asking them to register their choice. This led to a response rate of 33.0% in 2016, of which 73.9% gave permission for organ donation [2]. In other words, many adolescents did not make a choice regarding organ donation yet, or at least did not register this choice. This lack of registration leads to several problems, including the burden on family members and medical professionals when an unregistered individual dies. For example, when no donor record of a patient is found, the next of kin will be asked for consent. This is a stressful situation for all people involved and results in a high refusal rate [3–5]. To increase the registration rate, adolescents could be supported in making a well-informed decision and be encouraged to register this choice.

Reubsaet and colleagues made an effort to educate adolescents about organ donation and registration by designing an educational program for high school students. The main aim of their program was to increase the number of registrations, not necessarily the number of organ donors. The social cognitive theory (SCT) of Bandura was the main underlying theory during the development [6]. SCT describes three important factors that influence (intentions to participate in) a certain behaviour. These include people’s expected consequences of performing a certain behaviour (*positive/negative outcome expectations*), people’s expected social reactions to performing that behaviour (*social outcome expectations*) and beliefs about their own ability to perform this behaviour (*self-efficacy expectations*). Several determinant studies and pilot tests led to the development of the three educational components of the program: (1) videos to elicit discussion about positive and negative outcome expectations of organ donation and registration, (2) working with an interactive computer program with tailored feedback, and (3) practicing with completing a registration form [7–10]. This program was proven to be effective in increasing the intention to register in a large field study [11], after which the program was translated from a paper-based version into a web-based version. Web-based programs have high potential, as they can be effective in changing behavioural outcomes with low costs [12]. Moreover, web-based programs enable one to reach a large group of people with information that can be tailored to the individual [13].

Another desirable adaptation regards the target group of the program. As the original program was only used among high-school students, lower-educated students were not reached. Lower-educated students have left high school by the age of 16 (as opposed to 17–18 for higher-educated students) and usually continue their education at Intermediate Vocational Education (IVE) schools [14]. IVE schools typically teach lower-educated adolescents from the age of 16 until their early 20s. These adolescents are all about to receive the letter about organ donation or have received it recently. The need for a program about organ donation might even be higher for this group than for high school students, as studies have shown that lower-educated individuals have a less positive attitude towards organ donation than higher-educated individuals [15–17]. Moreover, the registration rate of lower-educated individuals is significantly lower than that of higher-educated individuals [18].

Adjustments had to be made to make the website suitable for lower-educated students as well. Firstly, textual changes were made, as students at IVE schools score lower on reading competencies than high school students; 20% of the students that start their IVE trajectory score even lower than the minimal reading level required for civic integration [19]. Therefore, adjustments were made to improve text comprehension. Moreover, the number of questions in the interactive computer program was decreased by half. This selection was made based on a preparatory study in the target group [20]. This study was conducted among 405 IVE students, using a questionnaire based on previous literature, identifying important beliefs regarding organ donation and registration. The selection of beliefs was based on their association strength with registration behaviour and intention and the extent to which there was room for improvement, that is, the extent to which mean scores on the beliefs are in the desired direction (e.g. in favour of organ donation registration).

Adapting the web-based educational program of Reubsaet and colleagues to lower-educated students and implementing it in IVE schools throughout the Netherlands could help reach a larger group of adolescents and therefore increase the number of registrations. As the program is now web-based and applied to a different target group, it is important to study its effectiveness. This will be done in a cluster randomized controlled trial (CRCT) with post-test only in IVE schools spread over the Netherlands. In addition, a process evaluation will be peformed to determine the quality of implementation during this trial. Combining an effect and process evaluation will give insight into the effects of the program and how these effects were achieved. This article gives an overview of the different components of the program and provides a detailed protocol for the anticipated evaluation study.

## Methods/design

### Aims

The effect evaluation aims to give insight into the effect of the program on behavioural determinants, the intention to register (as an organ donor) and the actual registration behaviour itself. Attitude, self-efficacy, social outcomes and knowledge will be assessed as behavioural determinants.

With the process evaluation we aim to gain insight into how the program was implemented. The process evaluation relies on four different data sources: questionnaires from students, logbooks, interviews with teachers and user data from Google Analytics. The use of data triangulation enables different data sources to complement one another. This provides an overview of the implementation of the educational components on six levels: *reach, dose delivered, dose received, fidelity, context * and *reasons for fidelity and dose*. These levels are inspired by the model of Steckler and Linnan [21]. Additional file 1 provides an overview of all constructs used, the definitions we use in this study and the instruments used to measure them.

### Description of the intervention

The web-based program consists of three main elements: video fragments followed by group discussions, quizzes with tailored feedback and an exercise to fill in an organ donation registration form. The website is hosted by SIDVO, which is a foundation that aims to develop, evaluate and distribute organ donation education. The elements will be provided to the students during two 50-min lessons at school. At the end of the program, students are expected to be able to make a well-informed decision about organ donation registration and will be encouraged to register this choice.

Lesson 1 consists of four video fragments followed by group discussions. Each video deals with an aspect of organ donation and registration in which both positive and negative outcome expectations are included. The videos are designed to elicit discussion among students about brain death, the possibility to help other people by donating your organs, discussing the subject with others and the importance of registering in general (from the perspective of medical professionals and family members). Teachers will be provided with a manual to facilitate discussion after each video in which students have the opportunity to share their opinions and beliefs. This activity aims to increase involvement, encourage positive beliefs and counterbalance negative beliefs.

Lesson 2 combines two program elements. First, students will individually work with the website. The website provides the participants with two quizzes. One quiz will mainly focus on students’ knowledge, while the other one will focus on their opinions. The knowledge quiz reveals a score on a scale from 1 to 10 and the correct answers to the questions after completion. In the opinion quiz each question will be followed by tailored feedback. Participants will receive information that is personally relevant and fits their needs. The main goal of the quizzes is to teach participants about organ donation and registration and give them tailored feedback on misconceptions they might have. The second part of the lesson will be spent on an exercise on completing an organ donation registration form in order to enhance self-efficacy. Students will be provided with a copy of an organ donation registration form or use a digital version, whatever option is most convenient. The aim is to give students an enactive mastery experience, which increases their self-efficacy and therefore increases the intention to fill in a real organ donation registration form.

### Study design

This article was written in accordance with the Standard Protocol Items: Recommendations for Interventional Trials (SPIRIT) checklist (Additional file 2). The effects of the program on registration behaviour, registration intention and beliefs regarding organ donation and registration will be evaluated in a CRCT with post-test only (see Figs. 1 and 2). The program will be offered to both the control and experimental groups. Students in the control group will complete the evaluation questionnaire before receiving the program, while the experimental group will do this after receiving the program. Differential attrition can be prevented, as all participating classes will receive the program. A post-test design prevents the risk of testing bias by priming students for the program by filling out the questionnaire beforehand [22]. The absence of a pre-test, however, might also threaten internal validity, since equivalence of the groups cannot be established. The threat of possible differences at baseline will be minimized by using a large number of randomization units and a proper randomization [23].

**Fig. 1 Fig1:**
[figure not shown]
Design of the evaluation study. *Questionnaire P* questionnaire process evaluation, *Questionnaire E* questionnaire effect evaluation, *Questionnaire F* questionnaire follow-up measurement

**Fig. 2 Fig2:**
[figure not shown]
SPIRIT figure

After agreement to participate, classes will be matched by members of the study team to improve the equivalence of the groups. The classes will be matched on study discipline, and matched classes will be from the same school. From each pair of matched classes, one class will be randomly assigned to the experimental condition, while the other class will then be assigned to the control condition. Teachers will be notified as to whether they have to hand out the questionnaire before or after delivering the program to students.

The implementation of the educational program will be evaluated using both qualitative (i.e. semi-structured interviews) and quantitative (i.e. logbooks, questionnaires, Google Analytics data) methods, both during and post-delivery.

### Procedure

The educational program will be provided by the teachers in IVE schools during regular classes. They will receive a link via e-mail prior to the start of the study. With this link, both teachers and students can reach the website. Before the first lesson, the control group will complete the effect evaluation questionnaire. All participants will then receive lesson 1, with the video fragments and group discussions. During the next session, they will both receive lesson 2a, the quizzes with tailored feedback, and lesson 2b, the exercise on completing an organ donation registration form. Teachers will have the freedom to provide the lessons whenever it fits their schedule, but we expect that in most cases lesson 2 will be delivered within 1 or 2 weeks after lesson 1. After the whole program is delivered, students in the experimental group will fill in the evaluation questionnaire. Six months after the implementation of the program, participating students (students from both the experimental and control groups) will receive a follow-up questionnaire during class to measure their registration behaviour. New control classes will then be recruited to compare the registration behaviour of students who received the program with that of students who did not. Data for the process evaluation will be gathered partly during the program delivery and partly after. During the program delivery, data will be collected on usage (e.g. by means of Google Analytics), while after the program delivery, reasons for particular usage behaviour will be assessed (e.g. by means of interviews). Moreover, students in the experimental groups will complete a process evaluation questionnaire after the program is delivered.

### Study setting, population and sample size

The program will be evaluated in a school setting. More specifically, IVE schools throughout the Netherlands will be invited to participate in the program through various channels. In particular, teachers teaching the course ‘Citizenship’ will be approached, as organ donation fits with the content of this course. IVE schools typically teach lower-educated adolescents from the age of 16 until the early 20s, but students from all ages are welcome. Older students will therefore be automatically included in the sample as well. Students in IVE can choose from a variety of disciplines, both manual and non-manual. There are four levels within IVE, but the educational level is generally low as opposed to college or university education.

As participants will be recruited via their schools, they are not approached individually. Therefore, no inclusion or exclusion criteria are set on the individual level. On the class level, only students in IVE levels 2, 3 and 4 are included in the study. Level 1 is also known as entry training. Students in this level did not graduate from high school; therefore, we cannot guarantee they will be able to participate properly in the program due to a large variety in cognitive abilities at this level.

Data from a preparatory study in the same target group [20] and the evaluation of a similar study in a slightly different target group [11] were used in simulations to calculate the sample size for the current study. The calculations were performed using a Monte Carlo simulation study with MLPowSim and are therefore not based on design effects, but on the expected percentage of registration in the control and experimental groups as well as the variances of the random effects from the logistic multilevel model and intraclass correlations (ICCs) [24]. The calculations were based on an expected increase in the primary outcome, expected class size, the ICC and the power of the test. The matching was not taken into account, as this will only increase the power. Therefore, the chosen power level (80%) is a safe choice [25]. A relative increase of 20% of the primary outcome was minimally expected based on the results of the study by Reubsaet et al. [11]. In the preparatory study, the average number of students per class was 16.2, of which 73.8% were not registered yet (our target group). The average cluster size is therefore 11.95, or 12 unregistered students per class. In order to be able to detect a difference of 20% with 80% power in a two-sided test with α = 0.05, taking into account an ICC of 0.02 at class level and 0.01 at school level, the required sample size is 12 schools, with an average of 10 classes per school and 12 unregistered students per class, leading to a power level of 0.839. However, as there is a high range of the number of students per class, the number of schools is increased by 15% [26], resulting in a minimum of 14 schools (and thus 140 classes, of which 70 are assigned to the control condition and 70 to the intervention condition, with a total of 1680 unregistered students).

### Ethical approval

The study was approved by the Ethics Committee of the Faculty of Health, Medicine and Life Sciences on 23 October 2017 (reference number [name]/231017) and registered at the Dutch Trial Register (NTR6771; http://www.trialregister.nl/trialreg/admin/rctview.asp?TC=6771). Participation of teachers and students is voluntary, and they will provide written (students) or verbal (teachers) informed consent. Participants will be informed about the study, the opportunity to withdraw their consent at any time and the anonymity of the study and will be provided with contact information in case they have any further questions.

### Measurements

Four different measurement instruments will be used to gather data; questionnaires from students, logbooks, interviews with teachers and user data from Google Analytics.

#### Questionnaires

All students will participate in the evaluation study by completing a total of two or three questionnaires depending on the condition: one for the process evaluation (questionnaire P; experimental condition only), one for the effect evaluation (questionnaire E) and one follow-up questionnaire (questionnaire F). For the process evaluation, only students in the experimental condition will receive a questionnaire (questionnaire P) in which they are asked to evaluate the program after the second session. This questionnaire will assess the *dose received* and *reasons for fidelity and dose*. *Dose received* will be measured by assessing their appreciation for the program. The appreciation of the program as a whole as well as the three components will be assessed by asking the students how much they learned from each component and how much they enjoyed working with the component. Also, *reasons for fidelity and dose* will be assessed by asking students what parts they liked and what parts could be improved.

The questionnaire for the effect evaluation (questionnaire E) will be completed before (control condition) or after (experimental condition) the program delivery. The primary outcome will be the students’ intention to register (yes/no). Students who answered ‘yes’ to this question will be asked to specify the decision they would like to make (registering as a posthumous organ and tissue donor, a posthumous donor for specific organs and tissues or a non-donor; leaving the decision to the next of kin; or leaving the decision to a specific person), which will be dichotomized into intention to become a donor or not. All students will also be asked about whether they already registered a decision (yes/no) and, if yes, the choice they made (see the above-mentioned options). Only unregistered participants will fill in the intention question. Additionally, questions are included to measure attitude, self-efficacy, knowledge and social outcomes. These behavioural determinants are the main focus of the educational program.

Finally, all participants will receive a follow-up questionnaire (questionnaire F) after a period of approximately 6 months to measure their registration behaviour. As official registration records are private, participants will be asked whether they registered their choice since receiving the program and, if so, what choice they registered.

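### Students who register during the program leave the primary analysis in the experimental arm only, which biases the effect toward the null by an unknown and possibly small amount

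*Protocol article*

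**What the plan says.** The Questionnaires section makes intention to register, answered yes or no in questionnaire E, the primary outcome. It then restricts who answers: "Only unregistered participants will fill in the intention question". The same questionnaire asks every student in both arms whether a decision is already registered and, if so, which one. The article describes no question in E about when the registration took place.

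E falls on different sides of the program in the two arms. Study design: "Students in the control group will complete the evaluation questionnaire before receiving the program". Procedure: "After the whole program is delivered, students in the experimental group will fill in the evaluation questionnaire". On the interval between the lessons, Procedure adds: "we expect that in most cases lesson 2 will be delivered within 1 or 2 weeks after lesson 1".

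According to Description of the intervention, students "will be encouraged to register this choice" at the close of the program. Lesson 2 contains a form exercise: "Students will be provided with a copy of an organ donation registration form or use a digital version".

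Statistical analyses takes the effectiveness data from E and lists registration behaviour at 6 months as a secondary outcome. It states that missing data do not affect the comparison of the two groups. Nothing in the article counts a student who registered during the program as a success, or defines the unregistered group by status before the program.

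**The concern.** Entry to the primary analysis depends on registration status at E. In controls that status is measured before the program. In the experimental arm it is measured after a program whose purpose is to change it. A student persuaded to register before E reports being registered, skips the intention item and leaves the denominator. Apart from contamination, the program cannot cause this among controls before their E.

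The students lost in this way would have answered yes, so their removal lowers the observed experimental proportion. The faster the program achieves its real goal, the smaller its measured effect on intention. A weak or null primary result would then be hard to interpret, because the share lost is not known.

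Nothing else in the article repairs this. Multiple imputation is planned for skipped items when adjusting for covariates, not for an outcome that is never asked. The Discussion names contamination as a cause of underestimation but not this selection. By the 6-month follow-up the original controls have had the program. The intended choice (donor or not) is asked only of students who answered yes on intention, so it inherits the problem.

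**Working it through.** **Inputs from Study setting, population and sample size.** 16.2 students per class, 73.8% unregistered; 20% relative increase; two-sided alpha 0.05; ICC 0.02 (class) and 0.01 (school); power 0.839 with 12 schools, 10 classes per school and 12 students per class; then 14 schools, 70 classes per arm, 1680 unregistered students.

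**Assumptions, not in the article.** Control intention rate pC, shown at 40%, 43% and 50%. Early-registration rate r, the share of initially unregistered experimental students who register before E, shown at 0, 2% and 5%. All of them would otherwise have answered yes.

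**The plan's own figures.** 16.2 × 0.738 = 11.96, about 12. 12 × 1.15 = 13.8, rounded up to 14 schools. 14 × 10 × 12 = 1680, or 840 per arm. These reproduce. The power of 0.839 cannot be checked directly, because no control rate is given. It is matched at a control rate of about 42 to 43%: the normal approximation gives it at 42.8% with design effect 1 + 11 × 0.02 = 1.22, and a simulation gives 0.840 at 42%. The figure is not shown to be wrong.

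**Bias.** With true experimental proportion pE = 1.2 × pC, the observed proportion is (pE − r)/(1 − r). The shortfall is r(1 − pE)/(1 − r), which is positive whenever r > 0 and pE < 1.

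**Power.** Both arms are present in each school, so the school component cancels and the design effect is 12 × (0.02 + 0.97/12) = 1.21. With n = 840 controls and 840(1 − r) experimental students, SE² = 1.21 × [pC(1 − pC)/840 + pObs(1 − pObs)/(840(1 − r))], and power = Φ(difference/SE − 1.96).

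Example, pC = 40%, r = 5%: pObs = (0.48 − 0.05)/0.95 = 0.4526, difference 0.0526, SE = √(1.21 × (0.2400/840 + 0.2477/798)) = 0.0269, ratio 1.96, power 0.50.

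| Control rate | r | Observed difference (points) | Share of effect lost | Power |
|---|---|---|---|---|
| 40% | 0 | 8.0 | 0 | 0.85 |
| 40% | 2% | 6.9 | 13% | 0.74 |
| 40% | 5% | 5.3 | 34% | 0.50 |
| 43% | 0 | 8.6 | 0 | 0.90 |
| 43% | 2% | 7.6 | 11% | 0.81 |
| 43% | 5% | 6.1 | 30% | 0.61 |
| 50% | 0 | 10.0 | 0 | 0.96 |
| 50% | 2% | 9.2 | 8% | 0.93 |
| 50% | 5% | 7.9 | 21% | 0.83 |

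These powers treat all 840 per arm as fully effective. The step from 12 to 14 schools was meant to offset unequal class sizes, so on the plan's own basis the starting point at about 43% is nearer 0.84 than 0.90. The differences in points do not depend on this.

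**Composite among all students** (registered or intends to register). Students per arm: 840/0.738 = 1138. Design effect at 16.2 per class: 16.2 × (0.02 + 0.97/16.2) = 1.29. Proportions are 0.262 + 0.738 × pC against 0.262 + 0.738 × pE.
- 40%: 0.557 against 0.616, 5.9 points, power 0.71.
- 43%: 0.579 against 0.643, 6.3 points, power 0.78.
- 50%: 0.631 against 0.705, 7.4 points, power 0.91.

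Early registrants count as yes, so these figures do not change with r. At each control rate the composite has slightly less power than the planned analysis at r = 2% and more at r = 5%.

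**The case against.** The best defence is that r is likely to be small. The gap of a week or two follows lesson 1, which is videos and discussion. The encouragement to register belongs to the end of the program and the form exercise to lesson 2, and the Discussion says intention is measured directly afterwards. The exercise is described as practice for a later, real form. The error is also conservative: it cannot create a benefit. This stands, and it limits the severity. It does not remove the defect, because the article does not bound r and describes no question that would reveal it. The article also does not expressly rule out that a digital form is actually submitted.

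Three stronger readings are tempting, and the documents do not support them.
- A reader might infer that the effect could vanish. The formula gives a zero difference at r = 0.2 × pC/(1 − pC), which is 13% for a control rate of 40%, 15% for 43% and 20% for 50%. Nothing in the article suggests registration on that scale between lesson 1 and E.
- A reader might infer that the comparison is no longer randomised. That follows only if r is above zero, and the departure grows with r.
- A reader might infer that the 73.8% unregistered rate fails and the sample size with it. At r = 3%, 12 students per class become 12 × 0.97 = 11.6, which is trivial. The harm comes from who is lost, not from how many.

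The remedy may also come late for some classes: Trial status says recruitment of classes was completed in June 2018.

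**Conclusion.** The point holds as a structural defect of unknown size. As written, the primary population is fixed by a variable measured before the program in one arm and after it in the other, and registrations made in between are dropped, not counted. The direction is toward the null whenever such registrations occur. Under a 20% relative effect, r of 2% removes 8 to 13% of the true difference and r of 5% removes 21 to 34%, for control rates from 50% down to 40%. Power at r = 5% ranges from 0.83 to 0.50. These figures rest on assumed control rates, an assumed r and the premise that early registrants would have answered yes. At r = 0 nothing is lost.

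This should be fixed. It is not fatal, because the bias is conservative, r may be small, and registration status is already collected from everyone at E.

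**What to change.** **Where E is still to be given.** Add one item for registered students: did they register before or after the class's first lesson? Define the primary population as students not registered before that lesson. Count as yes anyone who has registered since then or intends to register. Controls complete E before their first lesson, so their endpoint remains intention.

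**Where E has been given without the item.** Prespecify registered-or-intends among all students as a supporting analysis. It needs no new data. Report registration status at E by arm, so that readers can judge how large r may have been.

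**In both cases.** Keep intention among students unregistered at E as a described outcome.

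**Cost.** One questionnaire item and a changed definition of the primary endpoint, to be recorded as such. Registration timing is self-reported. The all-students version is diluted by the roughly 26% already registered: 5.9 to 7.4 points, with power 0.71 to 0.91 for control rates of 40% to 50%. At the lower control rates that is below the 80% target, so it suits a supporting role better than replacing the primary analysis.
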